### Analysis plan

The Biometrics and Clinical Data Systems Department at the China Academy of Chinese Medical Sciences will be responsible for the data management and statistical analysis of this study.

Demographic and baseline variables will be compared across treatment groups using Analysis of Variance (ANOVA) for continuous variables and the chi-square test for categorical variables. If the expected number of subjects within a specific category is sufficiently small, Fisher's exact test will be used in place of the chi-square test.

### Efficacy analysis

The primary efficacy analysis will be based on the full analysis set, defined as all randomized subjects who have baseline and at least one post-baseline efficacy assessment. OA trials are prone to dropouts related to treatment (e.g., inadequate response or intolerance) and because such dropouts will not be at random, thus standard imputation methods are inapplicable. Therefore, we will conduct sensitivity analysis described below wherein missing data are imputed to increasingly adverse degrees to explore whether the primary result still stands. As a supportive analysis, efficacy will also be assessed based on the per protocol set, defined patients in the full analysis set who have no major protocol violation. Statistical comparisons for total and subscale scores based on the WOMAC will be made using a repeated-measure mixed model with terms for treatment, day, center, and baseline value as covariate. The within-subject covariance structure will be assumed unstructured. Treatment-by-day and day-by-baseline interactions will be included in order to compare the treatment difference at each assessment time point as well as for the average across time points. The treatment difference and its 95% confidence interval will be estimated from this model. The same approach will be used for analyzing the Patient Global Assessment of OA condition and the Investigator Global Assessment of OA condition. A similar approach will be used for analysis of Patient and Investigator Global Assessments of response to treatment, but without inclusion of a baseline covariate and associated interaction terms.

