### Randomization

A total of 500 patients, 100 in each hospital, will be recruited from eligible patients. They will be randomly and blindly assigned to 5 different treating groups through the globally multicentre online randomization facility established by China Academy of Chinese Medical Sciences http://210.76.97.192:8080/cjbyj/.

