### Sample size

Sample size calculations were based on published data [5,14,16]. The mean differences in WOMAC scores before and after treatment with the integrative TCM approach, counter osteophytes capsule, Fufang Zijin patch, acupuncture and Tuina are 11 (SD = 5), 12 (SD = 6), 9.34 (SD = 4.09), 10.17 (SD = 3.85) and 8.89 (SD = 4.32), respectively. Using these data we estimated that 420 patients would be sufficient to give 0.8 power at 0.05 alpha level. Allowing for dropout, we plan to enroll 500 patients.

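### The primary model makes no allowance for variances that differ by arm; if the planning SDs carried over fully, the integrated-versus-capsule test would run at about 9.4% instead of 5%

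*Protocol article*

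**What the plan says.** The Efficacy analysis section of the protocol article sets out the primary model in some detail. It is a repeated-measures mixed model with treatment, day, center and baseline, plus treatment-by-day and day-by-baseline interactions. Treatment differences and their 95% intervals are to come from this model. On covariance it says: "The within-subject covariance structure will be assumed unstructured". It does not say whether the matrix is shared by the arms or estimated for each, and it names no standard-error or degrees-of-freedom method.

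The Sample size section gives mean before-after changes in WOMAC that "are 11 (SD = 5), 12 (SD = 6), 9.34 (SD = 4.09), 10.17 (SD = 3.85) and 8.89 (SD = 4.32), respectively", in the order integrated approach, capsule, patch, acupuncture, Tuina. It attributes them to three cited published sources. From them it concludes that "420 patients would be sufficient to give 0.8 power at 0.05 alpha level".

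Under Randomization, patients are "randomly and blindly assigned to 5 different treating groups". The allocation ratio is not printed; equal arms are assumed below.

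**The concern.** An unstructured matrix is flexible over days: it frees the Day 14 variance, the Day 28 variance and their correlation. It is not flexible over arms. Unless something more is specified, mixed-model software estimates one such matrix from all patients together and uses it for the standard error of every pairwise contrast.

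In a two-arm trial with equal arms, pooling is nearly harmless, because the pooled variance is the average of the two variances that matter. That protection is lost here. The variance used for integrated versus capsule is borrowed in part from three arms outside the contrast. If those arms are less variable, the standard error is too small, the interval too narrow, and the test rejects too often under equal means. More patients do not cure this.

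The contrast at risk is an important one. The Discussion gives the aim as showing that the integrated approach beats its single components, and in Table 3 the capsule is part of all eight treatment combinations. Integrated versus capsule is therefore the comparison that isolates what the other modalities add.

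**Working it through.** **The plan's own figure.** The protocol states no error rate for any single contrast, so there is none to reproduce. Its nearest figure is 420 patients for 0.8 power. A one-way five-arm ANOVA on the planning means and SDs needs about 220 patients and has 98% power at 420, so 420 is not reproduced that way. That is a separate matter. Here 420 serves only to give 420/5 = 84 per arm.

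**Inputs.** SDs from the Sample size section: integrated 5, capsule 6, patch 4.09, acupuncture 3.85, Tuina 4.32. Two-sided alpha 0.05. Assumptions: equal arms; one covariance for all arms; model-based standard errors; residual SDs equal to, or in the same ratios as, the planning SDs.

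**Step 1, pooled variance.** (25 + 36 + 16.73 + 14.82 + 18.66)/5 = 22.24, an SD of 4.716.

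**Step 2, ratio of model SE to true SE.** For arms 1 and 2 of equal size, ratio = sqrt[22.24 / ((s1² + s2²)/2)]. The arm size cancels.

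**Step 3, actual error.** 2 × (1 − Φ(1.96 × ratio)).

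| Integrated versus | (s1² + s2²)/2 | SE ratio | Actual two-sided error |
|---|---|---|---|
| Capsule | (25 + 36)/2 = 30.5 | 0.854 | 9.4% |
| Patch | (25 + 16.73)/2 = 20.86 | 1.033 | 4.3% |
| Acupuncture | (25 + 14.82)/2 = 19.91 | 1.057 | 3.8% |
| Tuina | (25 + 18.66)/2 = 21.83 | 1.009 | 4.8% |

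For the capsule contrast, coverage of the nominal 95% interval is 100 − 9.4 = 90.6%. Half of the error, 4.7% against 2.5%, is false superiority of the integrated arm.

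**Step 4, simulation under equal means.** With 100,000 runs each, the pooled-variance test of integrated versus capsule rejects in 9.5% at 84 per arm and 9.6% at 100 per arm. Arm-specific variances give 5.1% and 5.0%, and 4.9% to 5.1% for the other three contrasts. An ANCOVA with baseline and five centers (84 per arm, 8,000 runs, pooled residual variance) gives 9.1% for the capsule contrast. These simulations use one time point and complete data, so they approximate the repeated-measures model and are not a full replica of it.

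**Step 5, if only part of the SD spread is real.** Shrink each SD towards 4.716: s(w) = 4.716 + w × (s − 4.716), then repeat Steps 1 to 3 for integrated versus capsule.

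| Share w of the spread | Pooled variance | Variance needed | SE ratio | Actual error |
|---|---|---|---|---|
| 1 | 22.24 | 30.5 | 0.854 | 9.4% |
| 0.5 | 22.09 | 26.15 | 0.919 | 7.2% |
| 0.25 | 22.13 | 24.14 | 0.957 | 6.1% |
| 0 | 22.24 | 22.24 | 1 | 5.0% |

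**The case against.** **The protocol does not print that one covariance is used for all arms.** This is right. It is the default reading of the quoted sentence, not its wording. A statistical analysis plan that is not shown could set arm-specific matrices or robust standard errors, and silence on such detail in a journal article is not an error. The point therefore stands as an improvement to a specified model, not as a mistake in it.

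**The SDs need not describe this trial.** This also stands. They are before-after change SDs from separate published sources, used only for sample size, and the article does not say that they share a scale. Their spread may reflect different studies or populations. The model's residuals are adjusted for baseline and center, and all arms are randomized from one population. A reader might infer that the plan contradicts itself, or that the test has a true error rate of 9%. The documents support neither, because nowhere are these SDs put forward as the arm-level residual SDs expected here.

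**Only one of the four contrasts with the integrated arm is inflated.** True: the other three are slightly conservative, and the mean over all ten pairs is 5.1%. A reader should not infer general inflation. The conservative contrasts do not, however, offset an anti-conservative one, because each supports a separate claim.

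**Unequal dropout could make it worse.** With 70 capsule patients and 88 in each other arm, the capsule contrast would reach 10.2%. Nothing in the protocol supports that pattern, so it is no part of the conclusion.

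**A pooled unstructured matrix is standard and defensible.** It is. The argument for changing it is that protection costs almost nothing.

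**Conclusion.** The point holds conditionally. With a common covariance, model-based standard errors, equal arms and full carry-over of the planning SDs, integrated versus capsule would be tested at about 9.4% two-sided, while patch, acupuncture and Tuina would be tested at 4.3%, 3.8% and 4.8%. Over the range from no carry-over to full carry-over, the capsule contrast runs from 5.0% to 9.4%. Where in that range this trial falls cannot be known from the documents, so 9.4% is the upper end of the range and not an estimate. The arithmetic is secure; the carry-over of the SDs is not. This is a cheap improvement worth making before unblinded analysis. If the analysis plan already provides arm-specific covariances or robust standard errors, the point falls away.

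**What to change.** In the Efficacy analysis section, state that the unstructured Day 14/Day 28 covariance is estimated separately for each treatment arm, with Kenward-Roger or Satterthwaite degrees of freedom. Robust (sandwich) standard errors are an acceptable alternative. Apply the same choice to the WOMAC total, to the pain, stiffness and function subscales, and within each run of the sensitivity analysis.

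The cost is a line of wording and a line of code, with no extra patients or data. Two days need three covariance parameters, so five arms need 15 instead of 3: 12 more, against about 420 evaluable patients. If the variances prove equal, the loss is about 0.4% in the critical value, since a contrast then rests on roughly 84 + 84 − 2 = 166 degrees of freedom instead of about 420 − 5 = 415. If the planning SDs do carry over, the integrated-versus-capsule interval becomes wider by a factor of about 1/0.854 = 1.17, which is its correct width.

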### Intervention

On Day 0 (Visit 1), patients will begin treatment with either herbal drug, herbal patch, acupuncture, Tuina, or integrative approach. On Day 14, patients will return for an interim visit (Visit 2). On Day 28, the final visit will take place (Visit 3). Thus, the duration of treatment is 4 weeks.

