### Individually integrated Traditional Chinese Medicine approach

The approach consist of basic treatment of oral counter osteophytes capsule and varying use of Tuina, acupuncture and herbal patch based on the severity of patient's symptoms. The differing individually integrated TCM treatments are shown on the left column of Table 3. The treatment combination (called "approach content" in Table 3) used depends on the WOMAC characteristics as listed in the right column of Table 3. The baseline WOMAC determines the initial treatment, and the ongoing WOMAC later in the trial determines the later ongoing treatments in this arm of the trial.

**Table 3 T3:** Individually Integrated TCM approach for knee OA

Approach content	WOMAC scoring
counter osteophytes capsule	all scoring < 40 mm
counter osteophytes capsule + acupuncture	any one in 5 pain subscales ≥ 40 mm
counter osteophytes capsule + Fufang Zijin patch	any one in 2 stiffness subscales ≥ 40 mm
counter osteophytes capsule + Tuina	any one in 17 physical function subscales ≥ 40 mm
counter osteophytes capsule + acupuncture + Fufnag Zijin patch	both at least one in 5 pain subscales and at least one in 2 stiffness subscales ≥ 40 mm
counter osteophytes capsule + acupuncture + Tuina	both at least one in 5 pain subscales and at least one in 17 physical function subscales ≥ 40 mm
counter osteophytes capsule + Fufang Zijin patch + Tuina	both at least one in 2 stiffness subscales and at least one in 17 physical function subscales ≥ 40 mm
counter osteophytes capsule + acupuncture + Fufang Zijin patch + Tuina	at least one in 5 pain subscales and one in 2 stiffness subscales and one in 17 physical function subscales ≥ 40 mm

Patients in all arms are allowed paracetamol as rescue medication for breakthrough pain at a dose of 500 mg up to a maximum of 2 g per day. The use of rescue medication should not exceed 3 days in each week and should not be taken within 48 hours of a follow up visit. A count of returned tablets will be done at each visit.

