### Endpoints

The primary efficacy endpoint of the study will be Western Ontario and McMaster Universities Index of OA (WOMAC) [15] total score at Day14 and Day 28.

Secondary efficacy endpoints are : i) patient global assessment of response to treatment; ii) patient global assessment of OA condition; iii) WOMAC pain, stiffness, and physical function subscales; iv) investigator global assessment of response to treatment; v) investigator global assessment of OA condition; vi) TCM assessment of OA condition measured by syndromes questionnaire (Table 4); vii)SF-36 assessment.

**Table 4 T4:** Syndromes questionnaire for TCM assessment of knee OA condition

Tongue color (choose one with √ or note for others)					
pale tongue □ pale red tongue □	red tongue □		teeth-marked tongue □	others (please note)	

Tongue fur (choose one with √ or note for others)					

white fur □ yellow fur □	thin fur □		thin fur □	others (please note)	

Pulse diagnosis (choose one with √ or note for others)					

floating pulse □ sunken pulse □ slow pulse □	rapid pulse □ fine pulse □		slippery pulse □ string-like pulse □	others (please note)	

Knee joint situation (mark with √ for yes or no)					

morning stiffness	no □	yes □	cold pain	no □	yes □
pain of unfixed location	no □	yes □	stabbing pain	no □	yes □
joint swelling	no □	yes □	muscle atrophy	no □	yes □

Whole body situation (mark with √ for yes or no)					

easy to sweat at daytime	no □	yes □	easy to sweat at nighttime	no □	yes □
sloppy stool	no □	yes □	hard bound stool	no □	yes □
dry mouth	no □	yes □	profuse dreaming	no □	yes □
reddish yellow urine	no □	yes □	frequent urination	no □	yes □
vexing heat in the extremities	no □	yes □	poor libido	no □	yes □
deafness	no □	yes □	torpid intake	no □	yes □
dizzy vision	no □	yes □	tinnitus	no □	yes □
lack of strength	no □	yes □	somnolence	no □	yes □
lassitude of spirit	no □	yes □	inability to sleep	no □	yes □

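### The two global-response models could carry baseline WOMAC total as a covariate: a possible free gain in precision, not an error

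*Protocol article*

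**What the plan says.** The Efficacy analysis section specifies, for WOMAC total and subscale scores, a "repeated-measure mixed model with terms for treatment, day, center, and baseline value as covariate". It adds treatment-by-day and day-by-baseline interactions and an unstructured within-subject covariance. For the global ratings of OA condition it says: "The same approach will be used for analyzing the Patient Global Assessment of OA condition and the Investigator Global Assessment of OA condition". For the ratings of response it keeps the same kind of model, "but without inclusion of a baseline covariate and associated interaction terms".

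Three other places bear on the point:

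- Endpoints lists the response ratings among the secondary endpoints, as items i (patient) and iv (investigator). The patient items run "patient global assessment of response to treatment; ii) patient global assessment of OA condition". The primary endpoint is the "WOMAC) [15] total score at Day14 and Day 28".
- Intervention fixes when treatment starts: "On Day 0 (Visit 1), patients will begin treatment with either herbal drug, herbal patch, acupuncture, Tuina, or integrative approach".
- The section on the individually integrated approach shows that WOMAC is measured before treatment: "The baseline WOMAC determines the initial treatment". The primary model needs a baseline WOMAC value in every arm, so this measurement is not confined to the integrated arm.

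**The concern.** The sentence on the response ratings is an explicit model choice, so an analyst who follows it will fit no term for baseline severity. Dropping the outcome's own baseline is unavoidable, because that value does not exist. Dropping every measure of baseline severity does not follow from this, since a covariate may come from a different instrument.

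Two things are at stake, both on secondary endpoints. If baseline severity predicts rated response, the confidence intervals for the treatment differences will be wider than the collected data require. And if the arms differ by chance in baseline severity, the model has no term that allows for it.

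A link between severity and response is plausible. In the integrated arm, baseline WOMAC item scores decide whether a patient has the capsule alone or the capsule with up to three further treatments (Table 3). How strong the link is in this trial, the protocol does not say.

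**Working it through.** The protocol gives no standard deviation, effect or power for the response ratings, so there is no stated figure to reproduce. The check shows what one baseline covariate would gain or cost over a range of assumed correlations.

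**Inputs**

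- Evaluable patients: 420 (Sample size). With equal allocation to five arms, which is assumed, 420 / 5 = 84 per arm.
- Test: two-sided, alpha 0.05 (Sample size; Sensitivity analysis).
- r: within-arm correlation between baseline WOMAC total and the response rating. Not given; 0 to 0.4 is assumed.
- Power without the covariate: 0.80, an assumed starting point for illustration. The protocol makes no power claim for these endpoints.

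**Formulas**

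- Variance ratio, adjusted to unadjusted: 1 − r².
- Confidence-interval width ratio: √(1 − r²).
- Equivalent number per arm: 84 / (1 − r²).
- Power: Φ[(1.960 + 0.842) / √(1 − r²) − 1.960].

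**Results**

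| Assumed r | Variance reduction | CI narrower by | 84 per arm acts like | Power, from 80% |
|---|---|---|---|---|
| 0 | 0% | 0% | 84.0 | 80.0% |
| 0.1 | 1% | 0.5% | 84.8 | 80.4% |
| 0.2 | 4% | 2.0% | 87.5 | 81.6% |
| 0.3 | 9% | 4.6% | 92.3 | 83.6% |
| 0.4 | 16% | 8.3% | 100.0 | 86.4% |

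Example at r = 0.3: 1 − 0.09 = 0.91 and √0.91 = 0.954. Then 2.802 / 0.954 − 1.960 = 0.977, and Φ(0.977) = 0.836.

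**Cost if the covariate predicts nothing**

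Intercept, treatment (4) and center (4) use 9 parameters, which leaves 420 − 9 = 411 degrees of freedom. The covariate and its day interaction take two more, leaving 409. The residual variance estimate grows by about 411 / 409 = 1.005, or 0.5%. Gain and cost balance where (1 − r²) × 411 / 409 = 1, that is r² = 2 / 411 = 0.0049, or r of about 0.07. After this cost the variance ratios at r = 0.1, 0.2, 0.3 and 0.4 are 0.995, 0.965, 0.914 and 0.844.

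**The case against.** The strongest reply is that nothing here is wrong. The plan follows a consistent rule: an outcome it models is adjusted for that outcome's own baseline where one exists. Treatment begins on Day 0, so a response rating has none, and the sentence removes only a term that cannot be defined. Under randomisation the comparison without it is unbiased and keeps its error rate. The primary endpoint is adjusted for baseline. The gain depends wholly on an unstated correlation and is at most 2% of interval width for r up to 0.2. A response rating already asks the rater to judge change from the starting state, so a large correlation with starting severity cannot be assumed.

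All of this stands, and it limits the point. It does not remove it, because the reason given supports dropping the own-baseline term but not leaving out a severity covariate that is already to hand.

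A reader might infer more than the protocol supports:

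- *That the model is biased or invalid.* It is neither; only efficiency and chance imbalance are at issue.
- *That all adjustment is dropped, without reason.* Center remains, as do treatment, day and their interaction, and there is an evident reason for the omission.
- *That these two endpoints are treated differently from every other one.* The section names no model for SF-36 or the TCM syndromes questionnaire. An article may leave that to the full plan, so no uniform standard can be invoked.
- *That a loss of precision is established.* Without r it is only possible.
- *That baseline global OA condition is known to be available.* Its collection is implied by its own model but stated nowhere, which is why baseline WOMAC is the safer choice.

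**Conclusion.** This is a free improvement, not an error or a contradiction. The two response models are valid as written but forgo whatever precision, and whatever protection against chance imbalance in severity, baseline WOMAC could give. Over the assumed range of r from 0 to 0.4 the gain runs from nothing to a 16% fall in variance (interval 8.3% narrower). The price is about 0.5% in variance if baseline WOMAC turns out to be unrelated to response. The figures rest on a linear model, a common within-arm correlation and 420 evaluable patients. The primary endpoint and the sample size are untouched, so the priority is low.

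**What to change.** Amend the last sentence of the Efficacy analysis section. Suggested wording: *The patient and investigator global assessments of response to treatment will be analysed with the same mixed model; as these ratings have no baseline value, baseline WOMAC total score and its interaction with day will be the covariate terms in both models.*

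Name this one covariate for both models, so that no choice is left until the data are seen. It is measured before treatment, so adjusting for it is legitimate even though WOMAC item scores also steer the treatment content in the integrated arm. The change should be made before any comparison of outcomes by arm.

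Cost: one sentence. It needs no new data, visits or patients, and no change to the primary analysis.

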### Sensitivity analysis

In this analysis missing data for patients prematurely discontinuing from the trial (or for patients for other reasons not included in the full analysis set) are generated by random draw from the completer patient data, then adjusted as described below. The analysis is described for a situation where treatment A is statistically significantly superior to treatment B by the primary efficacy analysis. The treatment effect is the difference of the WOMAC change in the treatment A and the WOMAC change in treatment B. Call this treatment effect difference D. Four scenarios are investigated, corresponding to the loss of 25%, 50%, 75%, and 100% of the treatment effect difference. Patients that prematurely discontinued from treatment A will have their WOMAC change values determined by random draw (with replacement) from the treatment A completers, then these values are adjusted downward by 1/8*D, 2/8*D, 3/8*D, then 4/8*D, for the 1^st^, 2^nd^, 3^rd^, and 4^th ^scenario, respectively. Treatment B dropouts will have their random draw values adjusted upward sequentially by the same factors (1/8*D, 2/8*D, 3/8*D, then 4/8*D). The four scenarios, therefore, are:

#1-Assuming loss of 25% of the treatment effect; this is the least adverse scenario.

#2-Assuming loss of 50% of the treatment effect seen in completers.

#3-Assuming loss of 75% of the treatment effect seen in completers.

#4-Assuming loss of 100% of the treatment effect; this is the most adverse scenario.

Because the analysis involves stochastic variables, it will be repeated 100 times in order to better estimate the means and approximate 95% confidence intervals.

The following treatment comparisons will be performed based on the repeated measures mixed model and sensitivity analysis:i) Comparison at each of Days 0, 14, and 28;ii) Comparison of the Day 14 and 28 averages, using the time-averaged Day 14 and 28 scores estimated within the model framework;iii) Comparison of the average over all post-treatment days, using the time-averaged Day 14 and 28 scores estimated within the model framework;iv)All statistical tests will be two-sided. The primary endpoint and key secondary endpoints will be tested.

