### Withdrawal

A participant will be considered to have withdrawn from the trial when consent is revoked (except to ask permission for a determination of a final withdrawal visit WOMAC score) or if the participant cannot be contacted or located. If this occurs, no further assessments will be performed. Participants will not be withdrawn from the trial for protocol violations. Withdrawal due to adverse event should be distinguished from withdrawal due to insufficient response. When a subject withdraws due to a serious adverse event, the serious adverse event must be reported in accordance with the reporting requirements.

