## Discussion

The biggest limitation of this study is the lack of placebo control. It should be noted that the aim of this trial is not to estimate the efficacy of treatments used, but to demonstrate that individually integrated TCM approach is superior to individual component alone. This aim arises from clinical experience. The components of these treatments have been used for centuries. TCM has over 2000 years' application in China, usually as "one method applied in a whole course of treatment". However, even though the individual approach, based on different features of OA, is recommended, there is no evidence that it is superior to a treatment component used alone.

In an OA trial, a statistically significant result might be due to the dropout pattern rather than a true treatment effect, so we are attempting to collect data at the time of discontinuation to enable better comparisons of those completing versus those discontinuing. Additionally, we are conducting a formal sensitivity analysis using imputed data for discontinued patients to determine whether a positive result remains positive in scenarios where part or all of the treatment effect difference seen in the completers is lost in the dropout patients. To our knowledge, this is the first trial in a chronic symptomatic disorder to explicitly specify this type of sensitivity analysis to address trial dropouts.

Our results will be conditional on the population recruited, and the patients we recruited, requiring pain intensity of 20 mm or more on visual analogue scales (VAS), may have larger or smaller responses to treatment compared to those without such a restriction. For example, it was recently shown that use of a "flare" to define trial eligibility in OA alters, on average, response to treatment [17]. Another limitation is no double-blinding. Although it is difficult to carry out double-blinding in this design, we blind those clinicians conducting the assessments to decrease possible bias. The study also lacks long-term follow-up and evaluation. However, the duration chosen in the present study is consistent with acute OA flare episodes; and the study is long enough to document a rapid onset of a treatment modality and its efficacy sustained for 4 weeks. The protocol has a provision for rescue medication although its use is discouraged.

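### The dropout scenarios draw from completers without using the dropout's own observed WOMAC, so they can exceed the primary Day 28 estimate when the favoured arm loses more poor early responders

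*Protocol article*

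**What the plan says.** The Efficacy analysis section names inadequate response and intolerance as reasons for dropout and states that "such dropouts will not be at random, thus standard imputation methods are inapplicable". It promises a sensitivity analysis in which imputed values become progressively worse, to see whether the primary result survives. The primary model is a repeated-measures mixed model with baseline as covariate and unstructured within-subject covariance.

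The Sensitivity analysis section gives the procedure. It is described for a case where A has already been found significantly superior to B. Values for those who leave early "are generated by random draw from the completer patient data, then adjusted as described below". In arm A the source is that arm's own completers, sampled with replacement. The shift comes in four steps: "these values are adjusted downward by 1/8*D, 2/8*D, 3/8*D, then 4/8*D". In arm B the direction is reversed: "Treatment B dropouts will have their random draw values adjusted upward sequentially by the same factors". The last step is described as "Assuming loss of 100% of the treatment effect; this is the most adverse scenario".

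Elsewhere the plan seeks outcome data from patients who leave. The Withdrawal section allows a request for a "final withdrawal visit WOMAC score", and the Discussion says "we are attempting to collect data at the time of discontinuation to enable better comparisons". Neither section gives those scores a role in the imputation.

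**The concern.** A random draw from completers treats a dropout, before the shift, as a typical completer of the same arm. The plan itself expects dropouts to differ from completers. For a patient with a poor Day 14 score, the mixed model predicts a poor Day 28 value through the within-subject covariance. The sensitivity analysis ignores that score and puts in a completer's value, lowered by D/2 at most. On this point the stress test uses less information than the analysis it is meant to challenge.

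If such patients leave mainly from the favoured arm, the draw restores the completer selection that the mixed model had corrected. A positive Day 28 result could then be reported as robust in all four scenarios when none of them was harsher than the primary analysis.

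**Working it through.** **1. The plan's own percentages.** A dropouts are shifted by −kD/8 and B dropouts by +kD/8, k = 1 to 4. The A−B contrast among dropouts is D − 2kD/8 = D(1 − k/4), a loss of 25, 50, 75 and 100%. The stated figures are reproduced when D is the completer difference.

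**2. Where the harshest scenario puts dropouts.** In scenario 4 both arms' dropouts get the midpoint of the two completer means. If the Sample size section's changes for the integrated arm (11) and Tuina (8.89) are taken as completer means, this is (11 + 8.89)/2 = 9.945. An integrated-arm patient who left for inadequate response is credited with more improvement than the average Tuina completer. The same holds for any pair with A ahead.

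**3. Comparison with the primary model.** Let p be the dropout share and g the completer mean minus the mean that the model predicts for that arm's dropouts.

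- Scenario k: S_k = D − (kD/8)(pA + pB)
- Primary model at Day 28: D − pA·gA + pB·gB
- So S_k exceeds the primary estimate when pA·gA − pB·gB > (kD/8)(pA + pB). With equal dropout this is gA − gB > kD/4.

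**4. Illustration.** From the Sample size section: A = 11 (SD 5), B = 8.89 (SD 4.32), true difference 2.11, and implied dropout 1 − 420/500 = 16%. Assumed, because the documents do not give them: Day 14/28 correlation 0.6, normal changes, 16% in each arm, and every dropout leaving after Day 14. Baseline and centre are left out.

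If an arm loses its lowest 16% at Day 14, the cut is z = −0.994 with normal density 0.2433, and the completer mean rises by correlation × SD × 0.2433/0.84.

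- Rise in A: 0.6 × 5 × 0.2897 = 0.869, so gA = 0.869/0.16 = 5.43
- Rise in B: 0.6 × 4.32 × 0.2897 = 0.751, so gB = 0.751/0.16 = 4.69

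With pA + pB = 0.32, the scenarios are D × 0.96, 0.92, 0.88 and 0.84. Dropout here depends only on the observed Day 14 score, so the primary model's expected Day 28 value is 2.11 throughout.

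| Dropout pattern | Completer D | S1 | S2 | S3 | S4 |
|---|---|---|---|---|---|
| A loses poor responders, B at random | 2.11 + 0.869 = 2.979 | 2.86 | 2.74 | 2.62 | 2.50 |
| Both lose poor responders equally | 2.11 + 0.869 − 0.751 = 2.228 | 2.14 | 2.05 | 1.96 | 1.87 |
| Both random | 2.11 | 2.03 | 1.94 | 1.86 | 1.77 |
| B loses poor responders, A at random | 2.11 − 0.751 = 1.359 | 1.30 | 1.25 | 1.20 | 1.14 |

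The threshold agrees. In the first row gA − gB = 5.43 exceeds even 4 × 2.979/4 = 2.98. In the second row 5.43 − 4.69 = 0.74 exceeds only the scenario 1 threshold, 2.228/4 = 0.56.

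**5. Simulation.** With 300 trials per setting, 100 per arm and somewhat milder selection (completer D 2.85), the first pattern gave 2.07 for the primary model and 2.73, 2.62, 2.51, 2.39 for the scenarios. Scenario 4 exceeded the primary estimate in 93% of trials (68% at correlation 0.4, 99% at 0.8). When both arms lost poor responders but at 24% in A and 8% in B, the results were 2.14 against 2.74, 2.62, 2.50, 2.39. Taking D as the mixed-model difference left the pattern unchanged (2.12 against 2.79, 2.71, 2.63, 2.54 in the first pattern).

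**The case against.** The first row of the table assumes an asymmetry that the documents give no reason to expect. If the integrated approach works better, as hypothesised, dropout for inadequate response would tend to fall on the comparators, and the scenarios are then strongly conservative. Higher intolerance in the integrated arm could push the other way. This stands, and it limits the point to what can happen under particular dropout patterns.

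A reader might infer three stronger things that the documents do not support.

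- **An inflated false-positive rate.** The analysis is described for an already significant primary result, so it cannot create one. In a null simulation of the first pattern, the primary model favoured A in 2.6% of trials, and the primary model and scenario 4 together also in 2.6%. Scenario 4 overturned none of those false positives, so the harm is a weak check.
- **That observed Day 14 scores are overwritten.** The procedure is for missing data, so an observed Day 14 score is presumably kept. The effect then sits in the Day 28 contrast and is halved in the Day 14/28 average: for scenario 4 in the first row, (2.50 − 2.11)/2 ≈ 0.20.
- **That the confidence interval is too narrow.** The plan says the analysis is repeated 100 times but not how the interval is formed, so coverage cannot be judged.

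The illustration also lets dropout depend only on the observed Day 14 score, which makes the primary model unbiased by construction. It does not test the plan's wider worry about dropout that is not at random. Patients with no post-baseline score have no Day 14 value to use.

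None of this removes the core. Selective loss from the favoured arm is one form of the treatment-related dropout that the plan names as its reason for the analysis. Nor is this a detail left out of a condensed article: the draw source, replacement, shifts and number of repeats are all written down.

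**Conclusion.** The point holds as a limited one. The stated draw does not guarantee that each scenario is harsher than the primary analysis. Under the assumptions above (correlation 0.6, 16% dropout per arm, A losing its poorest Day 14 responders, B losing at random), scenarios 1 to 4 lie about 0.75 to 0.39 points above the primary Day 28 estimate of about 2.1, so the check can falsely reassure. With equal, similarly selective dropout, scenario 1 is about level with the primary estimate and scenarios 2 to 4 are below it. With random dropout, or with poor responders lost from the comparator, all four are below. The primary analysis and the trial's type I error are not affected.

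**What to change.** Impute missing Day 28 values within arm, conditional on baseline, centre and the patient's last observed WOMAC (Day 14 or withdrawal visit), and then apply the planned k/8·D shifts. Draw patients with no post-baseline score conditional on baseline and centre only. State whether D is the mixed-model or the completer difference.

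Each scenario then lies below the primary estimate by about (kD/8)(pA + pB). With D equal to the primary estimate of 2.11 and 16% dropout per arm, the reductions are 0.08, 0.17, 0.25 and 0.34, giving 2.03, 1.94, 1.86 and 1.77. This is approximate, because a withdrawal-visit score may add information that the primary model does not have.

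The change uses scores that the plan already collects or seeks. The cost is a revised paragraph and slightly more programming.
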